## Abstract

**Background:**

Approximately 70%-80% of kidney cancers are clear cell renal cell carcinomas (CCRCCs). Patient management is based on imaging (abdominal ultrasound and computerized tomography), surgical excision of the tumor, and pathological analysis. A tissue biopsy is therefore necessary to confirm the diagnosis and avoid unnecessary nephrectomy. For metastatic cancers, a tissue biopsy is essential for establishing the targeted therapy. This biopsy of tumor material is invasive and painful. Other techniques such as liquid biopsy would help reduce the need for tissue biopsy. The development of a simple biological test for diagnosis is essential. CA9 is a powerful marker for the diagnosis of CCRCC. Exosomes have become a major source of liquid biopsy because they carry tumor proteins, RNA, and lipids. Urine is the most convenient biological liquid for exosome sampling.

**Objective:**

The aim of this study (PEP-C study) is mainly to determine whether it is possible to detect urinary exosomal CA9 for the molecular diagnosis of CCRCC.

**Methods:**

This study will include 60 patients with CCRCC and 40 noncancer patients. Exosomes will be isolated from urine samples and exosomal CA9 will be detected by transmission electron microscopy, flow cytometry, and reverse transcription-quantitative polymerase chain reaction.

**Results:**

This study is currently underway with funding support from the CHU Saint-Etienne of France.

**Conclusions:**

We expect to demonstrate that urinary tumor exosomes could be a novel liquid biopsy to diagnose CCRCC and to guide clinicians in treatment decision-making.

**Trial Registration:**

ClinicalTrials.gov NCT04053855; https://clinicaltrials.gov/ct2/show/NCT04053855

**International Registered Report Identifier (IRRID):**

DERR1-10.2196/24423

## Introduction

Renal cell carcinomas are serious and common cancers [1]. Approximately 70%-80% of kidney cancers are clear cell renal cell carcinomas (CCRCCs). Patient management is based on imaging (abdominal ultrasound and scanner), surgical excision of the tumor, and pathological analysis. Approximately one-third of patients with CCRCC have a locally advanced or metastatic tumor at the time of diagnosis and nearly 30% of treated patients will develop secondary metastases [1]. Recent advances in imaging techniques have increased the detection of kidney tumors; however, not all tumors are cancerous, with 10%-15% of all kidney tumors being benign and 20%-30% of tumors smaller than 4 cm being benign [2]. A tissue biopsy is therefore necessary to confirm the diagnosis and avoid unnecessary nephrectomy. For metastatic cancers, tissue biopsy is also essential for establishing the targeted therapy. This biopsy of tumor material is invasive and painful. Alternative techniques such as liquid biopsy would help reduce the rate of tissue biopsy. Therefore, development of a simple biological test for diagnosis is essential.

The notion of liquid biopsy has been mentioned in recent publications [3]. Liquid biopsies are based on the detection of cancerous biomarkers in body fluids, mostly in the blood, but can also include the urine, saliva, or other fluid. Liquid biopsies are preferable to tissue biopsies because they are less invasive.

Exosomes are small nanoparticles that are secreted into the extracellular medium by different cell types [4,5]. We propose detecting urinary exosomes from patients with CCRCC. A urine sample would be preferable to a blood sample because of the anatomical proximity of the urine to the kidney tumor. Moreover, urine is the simplest biofluid that can be obtained. We and others have found that urine is an important target for the exploration of markers for renal diseases [6]. The tumor exosomes from CCRCC in the urine are particularly abundant because of the location of the tumor directly in contact with the urine. Our hypothesis is that tumor exosomes present in the urine of patients with CCRCC could be detected. Our aim is to develop a reliable technique for the detection of tumor exosomes in the urine of patients with CCRCC to explore their usefulness as a liquid biopsy of CCRCC.

## Methods

### Study Design

This is a descriptive study (PEP-C study). The investigators will provide eligible patients with an informative notice on the PEP-C study. Upon a patient providing written consent, 100 ml of urine will be collected in a sterile tube for each exosomal analysis. The study design is outlined in Figure 1.

**Figure 1 figure1:**
[figure not shown]
Outline of study. RT-qPCR: reverse transcription-quantitative polymerase chain reaction

### Study Population

There is no available publication in the literature to calculate the number of subjects required for this type of study. Thirty patients receive surgery for removal of CCRCC in our department per year. Therefore, we propose to study 60 patients over 2 years. In addition, 20 control patients without cancer in our department are expected per year. Therefore, we propose studying 40 controls over 2 years. Eligibility criteria for cancer patients and controls are listed in Textbox 1. The age of the control group will be determined in agreement with the average age of occurrence of the CCRCC patients included in the study.

Inclusion and exclusion criteria of participants.
**Inclusion criteria for patients**
Adult patient >18 years oldAll patients with a renal mass and scheduled for surgery (partial or total nephrectomy)Patients having accepted and signed the consent formPatients benefitting from social security

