### Sample Size and Statistical Analysis

A selected group of 60 patients with renal cancer and 40 control subjects will be included in the study (Figure 1). The aim of this project is to evaluate the feasibility of detecting tumor exosomes as a liquid biopsy for CCRCC. We assume a 90% assay feasibility rate, 5% unilateral α, 90% power, and 10% patient withdrawal before the initial assay. According to the one-step Fleming design, 60 patients are required. The assays of the 60 patients will be compared with those of controls to evaluate if the tumor exosomes could be cancer markers.

The diagnostic performance of tumor exosomes will be evaluated by receiver operating characteristic curves. The area under the curve will be determined with its 95% CI. Analyses will be performed using SAS 9.4.

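### The case group of 60 is defined three ways (any operated renal mass, renal cancer, CCRCC), so the article does not fix how many CCRCC cases it will have or who is scored as a case

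*Protocol article*

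**What the plan says.** The Protocol article describes the 60 in these ways:

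- **Textbox 1, inclusion criteria for patients:** "patients with a renal mass and scheduled for surgery". The exclusion criteria cover urine volume, urinary catheter and legal guardianship. None concerns histology.
- **Abstract, Methods:** "This study will include 60 patients with CCRCC and 40 noncancer patients".
- **Study Population:** the number comes from departmental volume, "Thirty patients receive surgery for removal of CCRCC in our department per year", taken over two years.
- **Sample Size and Statistical Analysis:** "A selected group of 60 patients with renal cancer and 40 control subjects will be included in the study", and then "The assays of the 60 patients will be compared with those of controls". The same section plans ROC curves and an AUC with 95% CI.
- **Study Objectives and Endpoints:** the primary objective concerns exosomes from CCRCC. The secondary objectives take clear cell cancer as the reference status, and the secondary endpoints compare CCRCC patients with controls.
- **Data Collection:** pathology results are recorded for patients.

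The Introduction warns that not every renal mass is a cancer: "10%-15% of all kidney tumors being benign" and "20%-30% of tumors smaller than 4 cm being benign". It puts CCRCC at 70-80% of kidney cancers.

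**The concern.** A renal mass listed for nephrectomy, a renal cancer and a CCRCC are nested populations, and the article uses one number for all three. Eligibility requires no histology, so enrolment as written runs on the widest of them. The article gives no rule for an enrolled patient whose mass proves benign or non-clear-cell, and no enrolment target above 60.

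One of two things follows if 60 is the number of masses enrolled. Either the other masses are set aside and the CCRCC group falls below the planned size, or they stay among the cases and the CA9 detection rate and AUC no longer describe CCRCC. Either way the main results are affected. The Discussion also plans to derive a cutoff for cancer detection from these data.

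**Working it through.** **Inputs from the article.** Benign share of kidney tumors 10-15%; CCRCC share of kidney cancers 70-80% (both Introduction). Expected rate 90%, one-sided alpha 5%, power 90%, withdrawal 10%, one-step Fleming design, 60 patients (Sample Size and Statistical Analysis). Thirty CCRCC operations a year (Study Population).

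**1. The plan's own 60.** The null rate p0 is not stated, so 60 cannot be derived from the stated inputs alone. The normal-approximation formula is

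n = [(z(0.95)·√(p0(1−p0)) + z(0.90)·√(p1(1−p1))) / (p1−p0)]², with p1 = 0.90.

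At p0 = 0.75, n = [(1.645·0.433 + 1.282·0.300)/0.15]² = 53.5, so 54, and 54/0.9 = 60. Nearby values do not fit: after withdrawal, p0 = 0.74 gives 54 and p0 = 0.76 gives 68. So 0.75 is a plausible back-calculation, but still an assumption.

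**2. CCRCC among 60 enrolled masses.** Share = (1 − benign share) × (CCRCC share of cancers).

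- Low: 0.85 × 0.70 = 0.595, and 60 × 0.595 = 35.7
- High: 0.90 × 0.80 = 0.72, and 60 × 0.72 = 43.2
- After 10% withdrawal: 54 × 0.595 = 32.1 to 54 × 0.72 = 38.9

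That is about 36-43 CCRCC, or 32-39 evaluable. If all 60 have renal cancer, as the statistics section words it, 60 × 0.70 to 60 × 0.80 = 42-48 are CCRCC (38-43 evaluable). If all masses were under 4 cm (20-30% benign), 60 × 0.70 × 0.70 to 60 × 0.80 × 0.80 = 29-38.

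**3. Enrolment needed if 60 counts confirmed CCRCC.** 60/0.72 = 83.3 and 60/0.595 = 100.8, so 84 to 101 masses. Thirty CCRCC operations a year imply 30/0.72 to 30/0.595 = 42 to 50 operated masses a year on the same rates, or about 83 to 101 in two years. The two agree.

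**4. Power if the CCRCC group shrinks.** This is conditional on p0 = 0.75, and on the assumed 90% meaning CA9 detection.

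| Evaluable n | Normal approximation | Exact binomial |
|---|---|---|
| 54 | 90% | 83% (reject at 47 or more) |
| 39 | 77% | 65% |
| 34 | 71% | 75% |
| 33 | 69% | 58% |
| 32 | 68% | 60% |

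Like for like, power falls from 90% to about 68-77% (approximate), or from 83% to about 58-75% (exact). The exact values move up and down with n because the rejection threshold is a whole number.

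**5. Illustrations if all 60 are scored as cases.** These rest on assumptions that are not in the article.

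- Suppose 90% of CCRCC and 10% of other masses are CA9-positive. The mixed rate is 0.595·0.90 + 0.405·0.10 = 0.576 to 0.72·0.90 + 0.28·0.10 = 0.676. With the rule of 47 or more of 54, power is below 0.1%.
- Suppose the true CCRCC-versus-control AUC is 0.85 and other masses score like controls. The observed AUC is 0.595·0.85 + 0.405·0.5 = 0.71 to 0.72·0.85 + 0.28·0.5 = 0.75.

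**The case against.** The strongest reply is that the article never says enrolment stops at 60 masses. The Abstract counts CCRCC, Study Population builds the 60 from CCRCC operations, and the statistics section speaks of a selected group. Step 3 shows that 60 confirmed CCRCC is within the department's volume. This stands: a reader might infer that the study will have only 36-43 CCRCC, but that holds only if 60 counts enrolled masses.

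Next, the objectives already use clear cell status as the reference, and pathology is collected. This also stands, and it makes the fix easy. It does not remove the conflict with a statistics section that compares all 60 with controls.

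The Introduction's rates are general, not this department's surgical case mix. It also describes biopsy as the way to confirm the diagnosis before nephrectomy, and such selection would lower the benign share. The article does not say how many patients are biopsied first, so the counts are approximate.

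A reader might also infer that power drops from 90% to 60-75%. The article does not support that. The null of 0.75 is assumed, and the comparison sets a stated 90% against exact values when exact power at 54 is already 83%. If the 90% means only that the assay works technically, non-CCRCC urine need not lower it and the power argument falls away.

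Finally, Figure 1 is not available here, and a full protocol or SAP may define the analysis set. Either could settle the intent. The eligibility, case label and size printed in the article would still conflict.

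**Conclusion.** The inconsistency is real and should be corrected. Eligibility, case label and comparison set refer to three different populations, and the article does not say which one the 60 counts.

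If it counts enrolled masses, about 36-43 CCRCC are expected, with 32-39 evaluable, on the Introduction's general rates and the stated 10% withdrawal. The planned size is then not delivered for CCRCC. If it counts confirmed CCRCC, 60 is reachable, but the implied 84-101 enrolments are not written down. If all 60 masses are scored as cases, CA9 detection and the AUC are biased as measures for CCRCC. The size of that bias depends on marker positivity in the other masses, which the article does not give, so the power below 0.1% and the AUC of 0.71-0.75 are illustrations only.

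The power loss in step 4 is likewise conditional, on a null of 0.75 and on the 90% being a CA9 detection rate.

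**What to change.** 1. In the Abstract, Study Population, Textbox 1 and Sample Size and Statistical Analysis, define the case set, and the denominator for CA9 detection and the AUC, as pathology-confirmed CCRCC. Use the pathology result already on the case report form.
2. Analyse benign and non-clear-cell masses as a separate group, apart from both the CCRCC cases and the controls.
3. State what the 60 counts:
   - **Confirmed CCRCC:** give the implied enrolment of about 84-101 renal masses, which fits the stated 30 CCRCC operations a year.
   - **Enrolled masses:** restate the expected CCRCC as about 36-43, and recompute power at 32-39 evaluable from the sponsor's own null rate.
4. In either case, state the null rate and whether the 90% refers to CA9 detection or to technical success of the assay.

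The cost is mainly wording, and case definition needs no extra procedure because pathology is already recorded. The first option means consenting and assaying more patients; the second means stating a smaller CCRCC group and, if the 90% is a detection rate, probably lower power.

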**Inclusion criteria for controls**
Adult patient >18 years oldPatients hospitalized in the urology department without a known cancerPatient having accepted and signed the consent formPatients benefitting from social security
**Exclusion criteria**
Insufficient volume of urine samplePatients with a urinary catheterPatients under court-ordered guardianship or curatorship

### Study Objectives and Endpoints

Since CD63, CD9, and CD81 are the common markers for exosomes, we will test these three markers for detecting urinary exosomes. CA9 and vascular endothelial growth factor receptor 2 (VEGFR2) are two markers for CCRCC, which are used as markers for tumor exosomes.

The primary objective of this study is to detect urinary exosomes from CCRCC using an exosome marker (CD63) and CCRCC marker (CA9).

The secondary objectives are to assess (1) agreement between identification of CD63+/CA9+ tumor exosomes and patient status (clear cell kidney cancer), (2) agreement between the identification of CD9+/CD63+/CD81+/CA9+ tumor exosomes and patient status (clear cell kidney cancer), and (3) agreement between the identification of CD63+/VEGFR2+ tumor exosomes and patient status (clear cell kidney cancer).

The primary endpoint of the study is to characterize patients for whom CD63+ and CA9+ exosomes are detected. The secondary endpoints are as follows: (1) percentage of CD63+/CA9+ exosomes in patients with CCRCC compared with that of controls, (2) percentage of CD9+/CD63+/CD81+/CA9+ exosomes in patients with CCRCC compared with that of controls, and (3) percentage of CD63+/VGEFR2+ exosomes in patients with CCRCC compared with that of controls.

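### The primary endpoint is a description of marker-positive patients, while alpha and power attach to an undefined assay feasibility rate, so meeting the Fleming criterion would not necessarily show that CA9+ exosomes are detectable in CCRCC

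*Protocol article*

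**What the plan says.** Under Study Objectives and Endpoints, the primary objective is to detect exosomes from CCRCC in urine by one exosome marker (CD63) and one tumor marker (CA9). The endpoint that follows is "The primary endpoint of the study is to characterize patients for whom CD63+ and CA9+ exosomes are detected". Marker percentages in CCRCC patients against controls are secondary endpoints.

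Under Sample Size and Statistical Analysis, the aim is given as feasibility: "The aim of this project is to evaluate the feasibility of detecting tumor exosomes as a liquid biopsy for CCRCC". The inputs come next: "We assume a 90% assay feasibility rate, 5% unilateral α, 90% power, and 10% patient withdrawal before the initial assay". The result is "According to the one-step Fleming design, 60 patients are required". The same section plans a comparison with controls and ROC curves with an area under the curve and its 95% CI.

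The inclusion criteria (Textbox 1) admit any patient with a renal mass who is scheduled for partial or total nephrectomy. Data Collection says that pathological results are recorded.

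**The concern.** A one-step Fleming design tests one proportion against a null value. It needs a numerator, a denominator and a definition of success. The stated primary endpoint has none of these: it names an activity, and its population is the patients who already tested positive. A detection rate cannot be estimated from positives alone.

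The quantity that was powered has a different name, and the endpoints section does not mention it. An assay can be feasible in the sense that a sample was obtained, exosomes were isolated and a valid reading was produced, whatever that reading says about CA9. On that sense the study could meet its criterion with a low CA9+ rate. On the other sense, feasibility as detection, the criterion would bear on the objective, but the written endpoint would still be something else.

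The Discussion makes a multicenter study depend on this pilot being successful, so the meaning of success has to be clear.

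**Working it through.** **1. Reproducing the plan's figure.** Stated inputs: expected rate p1 = 0.90, one-sided alpha 0.05 (z = 1.645), power 0.90 (z = 1.282), withdrawal 10%. The null rate p0 is not stated. The formula is

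n = [(1.645·√(p0(1−p0)) + 1.282·√(p1(1−p1))) / (p1−p0)]², with enrolled = n / 0.90.

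| Assumed p0 | n from formula | Evaluable | Enrolled |
|---|---|---|---|
| 0.70 | 32.39 | 33 | 33/0.9 = 36.7, so 37 |
| 0.75 | 53.46 | 54 | 54/0.9 = 60 |
| 0.80 | 108.66 | 109 | 109/0.9 = 121.1, so 122 |

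The stated 60 is reproduced at p0 of about 0.75. Reading 90% as the null does not reproduce it: p1 = 0.98 gives 79 enrolled and p1 = 0.99 gives 54. From here on, p0 = 0.75 is an assumption solved back from the stated N.

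**2. The exact success count at n = 54 and p0 = 0.75 (binomial).**
- At least 46 of 54: alpha 0.0525, slightly above 5%; power at 0.90 is 0.914.
- At least 47 of 54: alpha 0.024; power at 0.90 is 0.832.

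The strict rule is therefore at least 47. With 55 evaluable, at least 47 gives alpha 0.045 and power 0.906.

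**3. What the two readings would conclude from the same data.** The CA9+ shares are illustrative and not from the documents. The rule is at least 47 of 54, with 90% valid assays.

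| CA9+ share of valid assays | Overall detection rate | Expected CA9+ of 54 | P(rule met), success = valid assay | P(rule met), success = CA9+ detected |
|---|---|---|---|---|
| 50% | 0.90 × 0.50 = 0.45 | 24.3 | 0.832 | below 0.0001 |
| 75% | 0.90 × 0.75 = 0.675 | 36.5 | 0.832 | 0.001 |
| 90% | 0.90 × 0.90 = 0.81 | 43.7 | 0.832 | 0.17 |
| 100% | 0.90 | 48.6 | 0.832 | 0.832 |

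With 95% valid assays the valid-assay column becomes 0.995. Using at least 46 changes the figures (0.914 at 90% valid) but not the pattern. The readings agree only when every valid assay is CA9+.

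**4. Choice of denominator.** If patients who withdraw before the assay were counted as failures, 90% detection among those assayed would become 0.90 × 0.90 = 0.81 of all enrolled. With n = 60 and p0 = 0.75, the exact rule is at least 51 (alpha 0.045), and its power at 0.81 is 0.27. The sample size already allows for withdrawal, so the matching denominator is assayed patients.

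**5. How many of the 54 would have CCRCC.** The Introduction puts CCRCC at 70%-80% of kidney cancers and benign lesions at 10%-15% of kidney tumors. If the enrolled masses followed those figures, confirmed CCRCC would number from 54 × 0.70 × 0.85 = 32.1 to 54 × 0.80 × 0.90 = 38.9. Exact power at p1 = 0.90 and p0 = 0.75 would be 0.60 with 32 patients (at least 29) and 0.67 with 38 (at least 34). Exact power moves in steps; 34 patients (at least 30) would give 0.75. Study Population, however, counts thirty CCRCC operations a year, so the 60 may be meant as CCRCC cases only. In that case this shortfall does not arise.

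**The case against.** The best case for the plan is that feasibility means detection. The sentence just before the 90% assumption speaks of detecting tumor exosomes. The endpoints section says CA9 and VEGFR2 serve as the markers of tumor exosomes. The closing paragraph of the Discussion refers to the technical feasibility of detecting exosomal CA9 in CCRCC urine. This is a fair reading and may well be the intended one. A reader might infer from the endpoint wording that the Fleming test certainly concerns technical success, and that passing it could not show detection. The documents do not support that stronger claim. What remains is that no sentence equates the feasibility rate with CD63+/CA9+ detection, and that the endpoint is not a rate under either reading.

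A reader might also object that the primary test uses no controls. That is not a defect here. The study is called descriptive and a pilot, and a single-arm primary analysis with discrimination as secondary is legitimate. Controls enter through three secondary endpoints, the ROC analysis and the cutoff announced in the Discussion, where a non-specific signal should become visible.

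Third, a condensed article may leave the positivity threshold and the success count to a fuller document, so their absence alone is not the point. The point is that two items the article does state, the primary endpoint and the quantity powered, do not match. The descriptive label does not resolve this, because the article states an alpha and a power.

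**Conclusion.** The point holds in this form: the stated alpha and power do not attach to the stated primary endpoint, and meeting the criterion would not necessarily show that CA9+ exosomes are detectable in CCRCC. This follows from the text and needs no assumed figure.

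The size of the consequence does rest on assumptions, namely a null of 0.75 and illustrative CA9+ shares. Under them, the probability of success ranges from 0.83 to practically zero depending on which reading is applied.

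It would be wrong to conclude that 60 is miscalculated. It fits the formula at p0 of about 0.75, although with an unstated null the same inputs could give anything from 37 to 122 over the range 0.70 to 0.80.

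**What to change.** 1. Restate the primary endpoint as the proportion of assayed patients with pathology-confirmed CCRCC in whom CD63+/CA9+ exosomes are detected. Pathology is already collected.
2. Fix positivity from isotype or blank background before assay results are linked to patient status. A cutoff taken from this study's 40 controls would not be fixed in advance, and it would set the apparent specificity by construction.
3. State the null, the alternative and the exact success count for that proportion. If 0.75 and 0.90 are intended, the exact rule is at least 47 of 54 (power 0.832) or at least 47 of 55 (power 0.906).
4. Report technical assay success and withdrawal before the assay as separate feasibility rates. Keep the characteristics of positive patients as description and the comparison with controls as secondary.

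The cost is a rewording of the endpoint and sample-size paragraphs, with no new assays. The downside is that confirmed CCRCC cases may fall below 54 because all renal masses are eligible. The sponsor should then restate the power for the number expected, which may be lower than 90%, or say that recruitment continues until the required number of confirmed cases is reached.
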